**Methods:**

This monocentric adherence program consists of short, repeated motivational interviews focused on patients’ medication behaviors combined with the use of electronic monitors containing patients’ medications. When patients open the electronic monitor cap to take their medication, the date and hour at each opening are registered. In total, 73 patients are randomized as 1:1 in 2 parallel groups; the adherence program will last 6 months in the first group versus 12 months in the second group. After the intervention phases, patients continue using their electronic monitors for a total of 24 months but without receiving feedback. Electronic monitors and pill counts are used to assess medication adherence. Persistence and implementation will be described using Kaplan-Meier curves and generalized estimating equation multimodeling, respectively. Longitudinal adherence will be presented as the product of persistence and implementation and modelized by generalized estimating equation multimodeling. The evolution of the ADVANCE (Action in Diabetes and Vascular disease: Preterax and Diamicron Modified-Release Controlled Evaluation) and UKPDS (United Kingdom Prospective Diabetes Study) clinical scores based on medication adherence will be analyzed with generalized estimating equation multimodeling. Patients’ satisfaction with this study will be assessed through qualitative interviews, which will be transcribed verbatim, coded, and analyzed for the main themes.

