### Trial Design

The PANDIA-IRIS design uses a mixed approach as it combines (1) a monocentric, prospective, and open randomized controlled trial and (2) a qualitative study. Patients will be randomized 1:1 in 2 parallel groups; patients of group A will attend the medication adherence program for 12 months and patients randomized to group B will attend the program for 6 months. Satisfaction with this study will be evaluated with selected patients through a qualitative interview at the end of the intervention phase or at the end of this study, or at drop-out (Figure 1). The legend for Figure 1 is available in Multimedia Appendix 1.

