### Intervention

#### Use of the Electronic Monitor

In both groups, patients use electronic monitors for 24 months. Electronic monitors register the date and hour of each opening, which corresponds to the moment of the drug intake as long as both behaviors are consecutive. Nevertheless, one limitation of this tool is that patients could open the electronic monitor without taking the drug or swallowing it long after the electronic monitor opening. In order to limit this bias and before showing the electronic monitor data to the patient at each pharmacy visit, pharmacists check with the patients that each opening corresponds to the drug intake. They ask the patient about the usual lapse of time between each opening and the real time of the drug intake. The liquid-crystal display (LCD) screen on top of the electronic monitor cap resets at 3 AM each morning. Hence, each time the patient opens the electronic monitor cap, the LCD shows the number of cumulative openings until 3 AM on the next day. The LCD screen reminds the patient about whether the medication has been taken or not.

Drugs to monitor are prioritized based on the following algorithm, which we constructed based on side-effect profiles: (1) all oral antidiabetic drugs, (2) statins, (3) diuretics, (4) beta-blockers, (5) calcium antagonists, (6) alpha-blockers, (7) angiotensin-converting-enzyme inhibitors, (8) angiotensin II receptor blockers, and (9) aspirin. Moreover, in each class, eligible drugs taken more than once a day prioritize monitoring. The maximum number of monitored drugs is 6. Physicians can modify the treatments at any time. If a patient has to stop all the monitored drugs, he or she will stop the study but the data collected until then will be kept for analysis. If a drug is switched to another eligible drug, the new prescribed drug will be monitored.

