### Postintervention Monitoring Phase

After the intervention phase, patients will still use electronic monitors with their LCD screens, but their adherence data will be double-blinded. Patients will not receive any feedback or motivational interviews about their daily drug management. The clinical team will not obtain any adherence reports. Due to ethical reasons, if the medication adherence rate detected by the MedAmigo software is less than 30% for at least one drug for 2 consecutive pharmacy visits, the software will automatically notify the pharmacist, and the patient will stop the study and will be oriented to the routine IMAP. If a physician in charge of a patient explicitly asks to access the adherence data during the postintervention monitoring phase for clinically urgent and important reasons, the principal investigator will sign a permission form that will be included in the case report form, and the patient will stop the study. All the data collected until then will be kept for analysis. At 18 months after the inclusion, during the postintervention monitoring phase, blood and urine samples will be collected to determine the clinical values at this time point. Indeed, the frequency of blood and urine samples collection differs between patients, and collecting laboratory values for each patient at this precise time point will ensure consistency in the analysis.

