#### Secondary Outcomes

The ADVANCE and UKPDS clinical scores will be assessed and compared at baseline, 6, 12, 18, and 24 months after enrolment for patients with type 2 diabetes in both groups. The ADVANCE score indicates the risk of developing cardiac complications associated with type 2 diabetes within 4 years and estimates the risk of developing renal complications within 5 years or more than 5 years. The UKPDS score calculates the risk of fatal coronary heart disease or stroke in patients with type 2 diabetes with no antecedent cardiovascular disease. These scores are calculated on the following parameters: sex, ethnicity, smoking status, time since diabetes diagnosis, blood pressure, glycated hemoglobin, total and high-density lipoprotein cholesterol, atrial fibrillation, albumin in urine, abdominal circumference, and BMI [24].

During the postintervention monitoring phase, the number of patients with less than 30% adherence for at least one drug during 2 consecutive visits as well as the time-to-event will be compared between the groups. We will also describe implementation and persistence at 6 months and 12 months after the end of the intervention in both groups to explore the impact of the length of the intervention on adherence. Patient satisfaction regarding the program will be analyzed through qualitative interviews.

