The number of patients with adherence rates less than 30% in the postintervention monitoring phase for at least one drug during 2 consecutive pharmacy visits will be compared between groups with a chi-squared test or with Fisher exact test if the sample size is less than 5 patients. The statistician who will perform the analysis will not be aware of the group allocation until the data are completely frozen. Statistical analysis will be performed with the R statistical package (version 3.6, The R Foundation for Statistical Computing) [29].

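### Patients below 30% adherence are counted over 12 months in group A but 18 in group B, and the Fisher rule as worded cannot take effect

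*Protocol article*

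**What the plan says.** All places are in the protocol article.

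- **Trial Design** (lengths in months): "patients of group A will attend the medication adherence program for 12 months and patients randomized to group B will attend the program for 6".
- **Use of the Electronic Monitor:** "In both groups, patients use electronic monitors for 24 months". The abstract agrees: "After the intervention phases, patients continue using their electronic monitors for a total of 24 months but without receiving feedback".
- **Postintervention Monitoring Phase:** the flag is an adherence rate "less than 30% for at least one drug for 2 consecutive pharmacy visits". A flagged patient leaves the study and is referred to the routine programme.
- **Secondary Outcomes:** the planned group comparison names two quantities: "the number of patients with less than 30% adherence for at least one drug during 2 consecutive visits as well as the time-to-event will be". The same paragraph describes implementation and persistence at 6 and 12 months after the intervention ends, in both groups.
- **Data Analysis, Medication Adherence:** the number of flagged patients "will be compared between groups with a chi-squared test or with Fisher exact test if the sample size is less than 5 patients". No common window, person-time or other adjustment is attached to this test.

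**The concern.** The follow-up clock starts at enrolment and stops at month 24 for everyone, while the postintervention phase starts at month 12 in A and month 6 in B. A count over that phase gives B half as much time again in which to be flagged. A chi-squared test on the two proportions cannot separate a longer time at risk from a higher risk. The excess falls on the 6-month group, and the main hypothesis under Objectives is that the 12-month group does better. A significant result could therefore be read as support for the longer programme when the design alone produced it.

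The switch to Fisher's test depends on sample size. What decides whether chi-squared can be trusted is the expected cell count, which may be small here even though the groups are not.

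**Working it through.** **1. Inputs.** Programme length 12 months (A) and 6 months (B), from Trial Design. Monitoring 24 months, from Use of the Electronic Monitor. 36 per group, two-sided alpha .05, from Sample Size. 73 enrolled, from Results. The documents state no figure for the below-30% outcome. The 12-month flag rate in group A, written pA, is an assumption, varied from 5% to 30%.

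**2. The plan's own sample size.** It concerns the primary outcome and serves here only to supply 36 per group. The difference is logit(0.975) − logit(0.925) = 1.151 and the SD is 1.7, so n = 2 × (1.96 + 0.842)² × 1.7² / 1.151² = 34.2. That rounds up to 35 per group, or 70 in all, against the stated 72. Power at 36 per group is 81.9% by the normal approximation. The stated figure is reproduced.

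**3. Exposure.** A: 24 − 12 = 12 months. B: 24 − 6 = 18 months. Ratio 1.5.

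**4. Equal constant hazard in both groups.** pB = 1 − (1 − pA)^1.5. For pA = 10%: 1 − 0.9^1.5 = 14.6%, so expected counts at 36 per group are 3.6 and 5.3. Rejection rates come from exact enumeration of both binomial distributions. With equal groups the smallest expected cell is half the total flagged, so it is below 5 when fewer than 10 patients are flagged overall.

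| pA (12 months) | pB (18 months) | Ratio | Uncorrected chi-squared rejects | of which favouring A | Yates or Fisher rejects | Smallest expected cell below 5 |
|---|---|---|---|---|---|---|
| 5% | 7.4% | 1.48 | 6.7% | 5.9% | 1.0% | 98.7% of trials |
| 10% | 14.6% | 1.46 | 9.8% | 9.2% | 4.0% | 60.7% |
| 15% | 21.6% | 1.44 | 11.0% | 10.7% | 6.6% | 12.7% |
| 20% | 28.4% | 1.42 | 13.0% | 12.7% | 8.3% | 1.0% |
| 30% | 41.4% | 1.38 | 17.8% | 17.7% | 11.5% | 0.0% |

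**5. Equal windows.** With 12 months in each group, uncorrected chi-squared rejects in 3.8% to 5.8% over the same range of pA, split evenly between directions.

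**6. A window of months 12 to 24 since randomisation.** This looks like a natural alternative, because both groups are then off the programme. But group B patients flagged in months 6 to 12 have already left the study. With all randomised patients as denominator, B's expected proportion is (1 − pA)^0.5 − (1 − pA)^1.5:

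- pA = 10%: 0.949 − 0.854 = 9.5%, against 10% in A.
- pA = 20%: 0.894 − 0.716 = 17.9%, against 20% in A.

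The bias turns round, and 5.1% or 10.6% of group B (1 − 0.9^0.5 and 1 − 0.8^0.5), those who lapsed soonest after the programme, are counted as never flagged.

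**The case against.** **Time-to-event is already planned.** Timed from the end of the programme and censored at the end of follow-up, it handles 12 against 18 months. This stands, and an article need not name the test; log-rank is already named for persistence. But the comparison sits beside the count and does not replace it, so the chi-squared result would still be reported with its tilt.

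**Type I error.** A reader might infer that it is above 5% whatever the event rate. The documents do not support that. They give no event rate and do not say whether chi-squared carries a continuity correction. At an assumed 10% rate, Yates or Fisher rejects in 4.0% of null trials.

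**Visits at risk.** A reader might go further and count pairs of consecutive 3-monthly visits, 5 in B against 3 in A. At pA = 20% that would raise the uncorrected rejection rate to 18.7%. The 3-monthly schedule is given for programme visits (Medication Adherence Intervention), but Participant Timeline and Data Collection says follow-up uploads happen at medication refills. The number of occasions for a flag is therefore not fixed by the text.

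**Who is compared.** It is also tempting to say that patients who stayed 12 months in A are compared with patients who stayed 6 in B. The article gives no denominator for this count, so that is an inference.

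**Fisher wording.** The authors very probably meant small cell counts. That is a fair reading, but the rule as printed says something else.

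**Conclusion.** The point holds for the counts. The 12 against 18 months is fixed by the design, and with equal constant hazard it makes group B's expected number flagged about 1.4 to 1.5 times group A's. Using Fisher's test does not remove this. Whether the test's error rate exceeds 5% depends on the unknown event rate and on the version of the test, as the table shows. The figures rest on a constant hazard, 36 patients per group at risk and the assumed range of pA.

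The Fisher condition as written cannot arise with 73 patients, although at a 10% rate about 61% of trials would have an expected cell below 5.

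This is one secondary outcome. The primary t test and the sample size are untouched. It should be corrected before the data are unblinded.

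**What to change.** 1. **Main test:** make the time-to-event comparison the main analysis of this outcome, timed from the end of each group's programme, censored at the end of follow-up, by log-rank test.
2. **Count:** restrict it to the first 12 months after each group's programme ends (months 12 to 24 in A, 6 to 18 in B). Secondary Outcomes already uses this window for implementation and persistence.
3. **Supportive analysis:** apply the same below-30% definition to the monitor data of both groups over months 6 to 24 since randomisation, including all randomised patients. Group A is still on the programme until month 12, so this compares the two programme lengths as assigned rather than two postintervention phases.
4. **Window to avoid:** do not use months 12 to 24 since randomisation as the main window, for the reason in step 6 of the working.
5. **Small counts:** use Fisher's exact test when any expected cell count is below 5, or use it throughout.

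The cost is a change of wording; the monitor data are collected in both groups anyway. Group B flags after month 18 drop out of the count. The log-rank test loses nothing by this, since more than 12 months after the programme no group A patient is at risk for comparison.

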#### ADVANCE and UKPDS Clinical Scores

The changes in the ADVANCE and UKPDS scores during the 24-month study will be analyzed with generalized estimating equation multimodeling, considering collected covariables such as sociodemographic data, monitored treatments, and medication adherence.

#### Qualitative Study

Audio recordings will be transcribed verbatim, and a content analysis will be performed using MAXQDA (VERBI GmbH) software. The codes will be labeled and categorized into themes. To ensure the codification validity, 2 investigators will codify the verbatim transcription independently and discrepancies will be discussed.

#### Missing Data

Missing data will be clearly identified in the results tables and will not be computerized.

### Patient and Public Involvement

Patients or the public were not involved in the design, conduct, reporting, or dissemination plans of our research. Once the results of the PANDIA-IRIS study will be published, the included patients will be informed about the results through a summary flyer using lay language.

## Results

Patients’ recruitment began in April 2016, ended in October 2020, and it was a challenging task. Indeed, this study was introduced to all consecutive eligible patients (n=275). In total, 73 out of 275 patients accepted to participate (26.5%) and 202 (73.5%) patients refused. Most patients who refused to participate argued that they had developed satisfactory skills and habits in drug self-management over time and that this study would disturb their routine. For instance, most patients already used a weekly pill organizer and were not ready to replace it with electronic monitors. Nevertheless, investigators could not confirm that these patients had no adherence issue. A new quantitative and qualitative substudy has been planned to understand the sociodemographic and clinical variables that differ between the patients who accepted versus those who refused to participate. Qualitative interviews will be conducted with a representative number of patients who refused to participate to understand their personal reasons for nonparticipation in order to further improve the routine IMAP. Patient recruitment is completed, and sociodemographic and clinical data are prospectively collected for the included patients until October 2022. Data analysis will be performed and results will be submitted for publication in a peer-reviewed open access journal.

## Discussion

### Strengths of This Study

The PANDIA-IRIS study is the first study to analyze the impact of a pharmacist-led adherence program on long-term medication adherence and cardiovascular scores in patients with diabetes and renal impairment. This study is based on a robust methodology; patients use electronic monitors, often considered as close to the gold standard to assess medication adherence. Moreover, patients are included in the routine IMAP that already led to significant improvements in the medication adherence and clinical outcomes of other chronically ill patients [12,17,18]. The mixed methodology is another strength of this study; the qualitative satisfaction interviews led with a representative number of included patients will enable the research and pharmacy teams together to further adapt the program to the specific needs of patients having DKD.

### Limitations

This study has some limitations. First, patients are included for 24 months in this study, which is a relatively long period of time, thereby increasing the probability of change in regimen over time and dropouts. In addition, the adherence data analysis is complex as patients use more than 1 electronic monitor. However, complex medication adherence data analysis was previously developed by the investigators, and the statistician who will perform the analysis is an expert in this field. Secondly, we cannot exclude the Hawthorne effect during the first 6 weeks of this study, explained by the fact that participants might improve their usual medication adherence behaviors as they feel observed [30]. We will analyze adherence as a trajectory (longitudinal, repeated measures) and we will pay attention to this risk during our analysis. All limitations and their possible impacts on the results will be clearly depicted in the final publication.

### Conclusion

The PANDIA-IRIS study will provide crucial information about the impact of the medication adherence program on adherence and the clinical outcomes of the patients with DKD who are known for polypharmacy challenges and who are engaged in complex and multifactorial care. Monitoring medication adherence during the postintervention phase is innovative in this field. This analysis will help health care providers to better support medication adherence in patients with DKD.

## Appendix

Multimedia Appendix 1 Caption of the design of the PANDIA-IRIS study.

Multimedia Appendix 2 Schedule of enrollment, interventions, and data collection for the PANDIA-IRIS study.

Multimedia Appendix 3 CONSORT-eHEALTH checklist (V1.6.1).

## Abbreviations

ADVANCE: Action in Diabetes and Vascular Disease: Preterax and Diamicron Modified-Release Controlled Evaluation
DKD: diabetic kidney disease
ESRD: end-stage renal disease
IMAP: interprofessional medication adherence program
LCD: liquid-crystal display
MEMS: medication event monitoring system
PANDIA-IRIS: Patients diabétiques et insuffisants rénaux: un programme interdisciplinaire de soutien à l’adhésion thérapeutique
RedCap: research electronic data capture
UKPDS: United Kingdom Prospective Diabetes Study
